**Time Table**

|  | **Screening** | **Connection to AnapnoGuard System** | **Mechanically Ventilation**  **Period** | **After AnapnoGuard Disconnection** | **Post Clearance Follow-up Phone Information** |
| --- | --- | --- | --- | --- | --- |
| **Time line** | **During hospitalization in ICU** | **Up to 6 h from intubation initiation** | **Daily evaluation** | **48h post extubation** | **1 month following extubation** |
| **Informed consent** | x |  |  |  |  |
| **Inclusion criteria** | x |  |  |  |  |
| **Medical history** | x |  |  |  |  |
| **Chest x-ray** | x | X | x* | x |  |
| **Blood tests** | x | X | x | x |  |
| **Vital signs** | x | X | x | x |  |
| **Trap bottle secretions***** |  |  | x |  |  |
| **Oxygen saturation** | x | x | x | x |  |
| **Mechanical complication assessment**** |  |  |  | x |  |
| **Subject’s general condition** |  |  | x | x | x |
| **AE and SAE** |  | x | x | x |  |
| **Study deviation** |  | x | x | x |  |
| **Final statistical analysis** |  |  |  | x |  |
| **Study exit** |  |  |  | x |  |

* Chest X-ray will be done at baseline, 48 hours after intubation and whenever there is clinical suspicion for VAP

** Mechanical complications assessment will include: spirometry, fiber optic in selected ICUs and questionnaire regarding throat pain and hoarseness.

***Recording level of trap bottle secretions 3 times a day (per shift). Records – Images and or electronic record

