# 3. ENDPOINT PARAMETERS

## 3.1 Primary Endpoint Parameter

This study has primary endpoint - *rate of device related AE and SAE as a result of using AnapnoGuard 100 during mechanical intubation.* Thus, a subject's responsiveness is evaluated as following:

- A subject is considered a “success “on *safety* if no device related AE or SAE has occurred during intubation.

Serious adverse event are defined as adverse requiring operation and/or associated with prolongation of hospital stay. Serious adverse events occurrence will be compared to serious adverse events incidence in the control group of mechanically ventilated patients in intensive care units.

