## 6.2 Study Time Line

Study procedure will take place in the Intensive Care Unit, and will continue at least 48 hours following disconnecting from the AnapnoGuard system. Study duration for each subject depends upon mechanical ventilation duration, which will be defined by subject’s general condition (not depended upon study procedure). Altogether, study duration will be approximately 12 months, depending on subject recruitment rate.

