## 9.3 Guidelines to Determine the Relationship of an AE/SAE to the Study Device/Procedure

- Definite: The adverse event is clearly related to the investigational treatment.
- Probable: The adverse event is likely related to the investigational treatment.
- Possible: The adverse event may be related to the investigational treatment.
- Unlikely: The adverse event is doubtfully related to the investigation treatment.
- Unrelated: The adverse event is clearly NOT related to the investigational agent(s).

Potential Adverse Events that may occur during the study in both the study (AnapnoGuard) and control groups are related to hyper/hypo inflation of the ETT cuff and suction dysfunction. The Adverse Events are listed in the table below:

| **Potential Adverse Events** | | **Severity** |
| --- | --- | --- |
| Over inflation of the cuff resulting in: | Hoarseness / Throat pain | Mild |
| Tracheal Stenosis | Moderate - Severe |
| Tracheal rupture | Severe |
| Under inflation of the cuff resulting in: | Leakage detected by ventilator | Mild |
| Decrease in saturation | Mild - Moderate |
| Apnea | Severe |
| Suction Dysfunction resulting in: | Tracheal Edema | Mild |
| Mucosal Injury | Mild - Moderate |
| Tracheal Ulcerations | Moderate |

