## 9.6 List of Serious Adverse Events

Serious, procedure related adverse events include those events with one or more of the following outcomes:

- Death: The subject’s death is suspected as being a direct outcome of the adverse event.
- Life-Threatening: The subject was at eminent risk of dying at the time of the adverse event or it is suspected that the use of the device or continuation of the procedure would have resulted in the subject’s death.
- Hospitalization (initial or prolonged):The use of the device or procedure was associated with an adverse event that resulted in the subject’s readmission to the hospital (>24 hours) or the prolongation of a hospital stay by >24 hours beyond the standard of care in the specific site.
- Disability: The use of the device or procedure was associated with an adverse event that resulted in significant, persistent, or permanent change, impairment, damage, or disruption in a subject’s body function/structure, physical activities, or quality of life.
- Requires Intervention to Prevent Permanent Impairment or Damage of a Body Part and/or Function: The use of the device or procedure resulted in a condition that required medical or surgical intervention to preclude permanent impairment or damage to a subject.

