## 9.7 Clinical Management of Study Related Adverse Events

AEs will be clinically managed according to medical indications, Local Health Authority, GCP and the standard of care in the specific Medical Center. Subjects will be entitled for continuation of clinical follow-up and treatment until of their study related clinical problem has been resolved, even beyond the pre-defined 1 month follow-up period.

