**IV. Final Study visit - Close out monitoring visit**

Ensure Investigator understands the on-going responsibilities

1. Record archival practices for source documents & CRF’s after completion of the study - up to 15 years;
2. Follow-up of on-going Adverse Events - up to 30 days after completion of the study;
3. Notify the sponsor in the event of Health Authority inspection.

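### New adverse events are scheduled for recording only to 48 hours after extubation, although a 1-month call is planned and section 9.7 assumes a 1-month follow-up

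*Protocol*

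**What the plan says.** The last column of the Time Table is a phone contact timed at "1 month following extubation". One row is marked in it, the subject's general condition. The AE and SAE row is marked at connection, during ventilation and at 48 hours after extubation, and is blank at 1 month. Study exit and final statistical analysis are both marked in the 48-hour column, before the call.

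Elsewhere in the protocol:

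- Section 6.2 says that study procedures "will continue at least 48 hours following disconnecting from the AnapnoGuard system". It does not mention the call.
- Section 9.7 entitles subjects to care for study-related problems "even beyond the pre-defined 1 month follow-up period".
- Section 9.6 counts as a serious outcome an event leading to "readmission to the hospital (>24 hours) or the prolongation of a hospital stay" by more than 24 hours beyond the site's standard of care.
- Section 9.3 lists "Tracheal Stenosis" among the potential events of cuff over-inflation, graded moderate to severe.
- Section 3.1 defines a subject as a success "if no device related AE or SAE has occurred during intubation", and adds that SAE occurrence will be compared with the control group.
- Sections 3.2 and 6.8 set the assessment of mechanical complications within 48 hours of extubation.

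**The concern.** The protocol describes itself as a safety study and plans to contact patients at 1 month, yet the schedule does not use that contact to ask about adverse events. It also places study exit before the contact, while section 9.7 treats 1 month as the follow-up period. The two places give different answers to when a subject's follow-up ends.

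Two things are at stake. First, sites cannot tell whether an event learned of at the call belongs in the CRF as an AE. Some may record it and others not, and in an open-label trial such discretion could differ between arms. Second, the SAE comparison with control in section 3.1 would stop at a point where some of the protocol's own SAE criteria often cannot yet be judged.

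**Working it through.** No sample size, power or event count enters this point, and the protocol states no figure to reproduce. The check sets the relevant texts side by side.

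**Step 1. What is scheduled after 48 hours.**

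| Time Table row | 48 h post extubation | 1 month (phone) |
| --- | --- | --- |
| Subject's general condition | marked | marked |
| AE and SAE | marked | blank |
| Study exit | marked | blank |
| Final statistical analysis | marked | blank |

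Scheduled AE/SAE recording ends at 48 hours. The last scheduled contact is at 1 month.

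**Step 2. Whether another section extends recording of new events.**

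- Section 9.4 requires AEs to be recorded during the course of the study and captured at every subject visit. The Time Table has the subject exit at 48 hours, and nothing says that a later phone call counts as a visit.
- Section 9.4 also follows events until resolution, and section 10.3 (part IV) provides for "Follow-up of on-going Adverse Events - up to 30 days after completion of the study". Both concern events already identified. They are compatible with a 48-hour window for new events and do not lengthen it.
- Section 9.7 concerns entitlement to care for study-related problems. It assumes a 1-month follow-up period but schedules no inquiry.
- Section 6.2 gives a minimum of 48 hours after disconnection, so it neither rules out the call nor provides for it.

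None of these schedules ascertainment of new AEs or SAEs between 48 hours and 1 month. Only section 9.7 actually disagrees with the Time Table's study exit.

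**Step 3. Which protocol-defined events fall in the gap.** A patient must be discharged before being readmitted, and a stay can be called prolonged only once it has run past the expected length. For ICU patients 48 hours after extubation, often neither can be determined. Section 9.6 makes both SAE outcomes, section 9.2 also lists prolonged hospitalization and rehospitalization, and section 3.1 names prolonged stay in its own SAE definition. Airway symptoms that begin after 48 hours are in the same position.

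**Step 4. Which endpoints are touched.**

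| Result | Window in the protocol | Affected? |
| --- | --- | --- |
| Primary success proportion (3.1) | during intubation | no |
| Mechanical complications (3.2, 6.8) | 48 h after extubation | no |
| SAE comparison with control (3.1) | no end point stated; recording scheduled to 48 h | yes, truncated |
| AE tabulation by arm (8.1) | no end point stated; recording scheduled to 48 h | yes, truncated |

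**The case against.** The strongest reply is that the protocol's questions are narrower than safety at large. The primary objective is safety during ventilation and intubation, the primary endpoint is limited to intubation, and the mechanical-complication endpoint is set at 48 hours. The schedule covers both endpoint windows, so a longer window is partly a design preference. This stands as far as those endpoints go. It does not explain why a call is scheduled without AE questions, nor why section 9.7 assumes a follow-up period that the Time Table closes at 48 hours.

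A reader might infer that the trial cannot detect the serious cuff-related harms it names. The documents do not support that. Section 9.3 also lists tracheal rupture and apnea, both graded severe, as well as mucosal injury and tracheal ulcerations, and nothing places these after 48 hours. Spirometry and, in selected ICUs, fiber-optic examination are scheduled within the window. The protocol gives no onset times, so the view that stenosis appears later is clinical reasoning from outside it.

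A reader might also infer that later events are lost altogether. That is too strong. General condition is asked at 1 month, and events already open are followed. The exact statement is that new events are not scheduled to be recorded as AE/SAE.

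Finally, the final-analysis mark sits in a per-patient column and cannot mean that the trial is analysed 48 hours after each extubation. It is weak evidence about analysis timing, and the point does not depend on it.

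**Conclusion.** The point holds as a gap in the schedule and an internal inconsistency. From 48 hours to 1 month after extubation, new AEs and SAEs have no scheduled record in either arm of the 60 planned patients. The Time Table and section 9.7 disagree on when follow-up ends. The consequence is a truncated safety profile and a truncated SAE comparison with control, mainly for readmission, prolonged stay and late airway symptoms. The primary endpoint and the 48-hour secondary endpoint stand as written.

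The number of events involved cannot be derived. The protocol gives no rate for events after 48 hours, and the share of calendar time outside the window is not a measure of risk. The conclusion rests on the Time Table as printed and on the argument that readmission and prolonged stay often cannot be established within 48 hours of extubation. It does not rest on any assumed onset time for stenosis. It is a modest point, worth acting on because the contact is already planned.

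**What to change.** 1. In the Time Table, mark AE and SAE in the 1-month column for both arms. Give the call set questions on death, readmission, prolonged stay and airway symptoms, with relatedness assessed as in section 9.3.
2. Move study exit to that call, and place the final analysis after the last patient's call.
3. Reconcile the Time Table with sections 6.2 and 9.7 on when follow-up ends, and describe the call in section 6. Count time from extubation in both arms, since section 6.2 counts from disconnection from a device that control patients do not have.
4. Report events between 48 hours and 1 month by arm as a descriptive safety result, separate from the primary endpoint, whose definition does not change.

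The cost is a few questions on an existing call, one CRF page, and a final analysis no earlier than one month after the last extubation. One limit remains: a call can detect deaths, readmissions and symptoms, but it cannot itself establish tracheal stenosis.

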**Study Synopsis**

| **Study title** | **The safety of using AnapnoGuard 100 in intubated critical Care patients** |
| --- | --- |
| **Study number** | Protocol # **HST- AG­– 04**;Version 1.1 |
| **Sponsor** | Hospitech Respiration Ltd. |
| **Study design** | Prospective, single - center, double-arm, randomized-controlled open label, safety study. |
| **Recruitment duration** | Estimated recruitment duration: approximately 12 months. Study duration for each subject depends upon mechanical ventilation duration, which will be defined by subject’s general condition. |
| **Study site** | The study will be conducted at the ICU of the Università Cattolica del Sacro A Gemelli University Hospital, Rome, Italy. in Rome. Additional ICU may be added. |
| **Principal Investigator** | Professor [name], Director of the institute of Anaesthesiology and Intensive care. |
| **Investigational product** | Intended Use/Indications for Use:  ***AnapnoGuard™ 100 Respiratory Guard*** Systemis intended for airway management by oral/nasal intubation while providing continuous endotracheal cuff pressure control using non-invasive measurement and monitoring of carbon dioxide concentration in the subglottic space and evacuation of secretions from above the endotracheal tube’s cuff.  The system is comprised of the following main three components:   1. AnapnoGuard 100 control unit 2. Single use AnapnoGuard endotracheal tube with two suction lumens and a vent lumen 3. Single use AnapnoGuard interface harness and filters kit |
| **Patient population** | Patient admitted to ICU and expected to receive mechanical ventilation for at least 12 hours. Patient will be randomly assigned to study or control group using the block randomization method. |
| **Patient selection criteria** | **Inclusion Criteria**  Subjects eligible for this clinical study must fulfill **all** of the following:   1. Age above 21 (men and woman); 2. Patient is admitted to ICU and expected to receive mechanical ventilation for more than 12 hours; 3. Absence of clear signs of pneumonia and lung contusion on chest X ray; 4. Connection of the ETT to the AnapnoGuard system less than 6 hours from intubation initiation; 5. No fever or fever from known from other non chest/lung origin;     **Exclusion Criteria**  Subjects not eligible for this research study include those that **have any** of the following:   1. Patients who had been treated with mechanical ventilation during the last 3 months; 2. Patients with facial, oropharyngeal or neck trauma 3. BMI>40 4. Pregnant women 5. Patient ventilated in prone position  Difficult intubation (defined as more than 3 intubation attempts) |
| **Primary objectives** | The study primary objective is:   - Evaluation of the safety of using the AnapnoGuard 100 system during the course of mechanical ventilation and intubation in Intensive Care Unit (ICU); |
| **Secondary objectives** | The study secondary objectives are   - Evaluate the occurrence of mechanical complication due to ETT cuff over inflation. - Physician satisfaction from AnapnoGuard 100 system |
| **Primary outcome measures** | Primary safety outcome measure in this study is:   - Rate of AE (adverse events) and SAE (serious adverse events) while using the AnapnoGuard 100 system during the course of mechanical ventilation and intubation in Intensive Care Unit (ICU). |
| **Secondary outcome measures** | - - Mechanical complication occurrence due to ETT cuff over inflation will be evaluated by the following measures during the 48 hours post extubation:   - Throat pain level, associated with the mechanical ventilation. Pain level will be assessed by VAS (visual analogue scale) Scale;   - Hoarseness occurrence   - Spirometry analysis   - Fiber optic analysis (this measure will be used in selected ICUs) - Medical staff satisfaction from AnapnoGuard 100 system will be established by designated questionnaire. |
| **Other Observation** | - Evaluation of the effect of AnapnoGuard system upon ventilator associated pneumonia (VAP) occurrence rate and time to VAP in intubated patients in intensive care units (ICU). |
| **Definition of the safety of AnapnoGuard system** | This study has primary endpoint - *rate of AE and SAE as a result of using AnapnoGuard 100 during mechanical intubation.* Thus, a subject's responsiveness is evaluated as following:   - A subject is considered a “success “on *safety* if no device related AE or SAE has occurred during intubation. |
| **Sample size** | Presentation of sample size is based on achieving 80% power overall to demonstrate that the *rate of AE and SAE as a result of using the AnapnoGuard 100 during mechanical intubation* is up to 0.20. Thus, the determination of sample size in this trial will be based on *rate of AE and SAE as a result of using AnapnoGuard 100 during mechanical intubation*.  A former study using *AnapnoGuard 100* during mechanical intubation in ICU revealed **no related AE or SAE** (all together 29 patients were studied). Consequently, we feel that 80% (of study patients with no AE or SAE during intubation) to be an appropriate clinical target for AnapnoGuard 100 success rate. Assuming a true success rate of 80%, a sample of **N = 25** will provide 80% power to show that AnapnoGuard 100 success (no AE or SAE during intubation) is at least 80%. This is based on a power analysis using the normal approximation for the binomial, with one-sided Alpha=0.05.  As control treatment is assumed to have the same success rate (at least 80% cases with no AE or SAE during intubation), same number of patients will be recruited to the control group **(N=25)**  To account for an approximate 15% dropout rate, we set a total number of patients N=**60** (for study and control groups together). |
| **Primary endpoint and study hypothesis** | For the primary endpoints we will compute Overall Proportion of Success:    The following hypotheses are specified:  The safety proportion of success (*No AE or SAE while using AnapnoGuard 100 during intubation* -R):  H0: R < 0.80  H1: R > 0.80  This hypotheses will be tested by:   1. Constructing a one-sided, lower 95% confidence interval about the observed Overall Proportion of Success in the relevant cohort; 2. Examining whether the lower limit of the confidence interval is at or above the success criterion   Study success will be declared if the following is met:  Lower confidence limit of *No* *device related AE and SAE as a result of using AnapnoGuard 100 during mechanical intubation* success rate is at 0.80 or above |

# Clinical background

Appropriate endotracheal tube (ETT) cuff inflation is an important part of the management of mechanically ventilated patients (1-5). An appropriately inflated ETT cuff should achieve isolation of the lower airways, thus reducing the risk of aspiration around the cuff and possible ventilator-associated pneumonia (VAP) (5–10). However, an over-inflated cuff may cause local mechanical complications such as mucosal ischemia, ulcerations, granulomas, tracheal stenosis, and tracheoesophageal fistulae (1– 5). Consequently, appropriate pressure maintenance of the ETT cuff is recommended in the guidelines (11).

The routine management of cuff inflation consists of periodic manual checking of the Pcuff (Intra Cuff Pressure), which does not ensure the appropriate maintenance of the Pcuff, during continuous tracheal intubation (5, 12). Moreover, the manual checking of the Pcuff may cause either over inflation or over deflation of the cuff that may cause aspiration of contaminated secretions to the lower airway during the maneuver (5, 12). Several devices that provide an automatic and continuous effective control of the Pcuff have been described in the literature. Even though, the automatic devices may provide effective continuous control of the Pcuff, they do not reduce rate of mechanical complications, such as tracheal hyperemia or hemorrhages, and they do not improve the rate of VAP, ICU mortality, or hospital mortality (13, 14). The main drawback of all these devises is that they cannot predict the true optimal cuff pressure for the specific patient so the target cuff pressure is being set arbitrarily for all patients.

The AnapnoGuard system (Hospitech Respiration LTD., Petach-Tikva, Israel) is an innovative respiratory guard system that continuously monitors and controls the cuff pressure. The optimal cuff pressure is being set by measurements of CO2 levels above the cuff (15). The optimal ETT cuff pressure is the minimal pressure needed to prevent CO2 leakage from the lungs to the oropharynx. Since the method is non-invasive (using a dedicated line in the ET tube), the optimal cuff pressure can be determined continuously as long as the patient is intubated. In a previous study, including elective surgical patients, the cuff pressure set by anesthesiologists was accurate in only 15% of the patients (15). During surgery, a new leak was created around the ETT cuff, as measured by CO2, developed in 27% of the patients. This leak was attributable to variable causes such as increased peak inspiratory pressure by >5 mm Hg caused by laparoscopic surgery with abdominal gas inflation, light anesthesia or inadequate neuromuscular blockade, changes of head positions, and ETT movement during surgery. In the ICU, patients are under prolonged mechanical ventilation with daily or even hourly changes in ventilation parameters, patient position, intra-abdominal pressure and degree of anesthesia.

A pilot study was performed with the AnapnoGuard system in two general ICU departments in Bucharest, Romania. A total of 29 patients were intubated with the AnapnoGuard tube and were connected to the AnapnoGuard System. Of the 29 patients, 17 patients were connected to the system under a clinical routine practice, as the AnapnoGuard 100 is cleared for marketing thought Europe (CE cleared). 12 patients were enrolled into the study. Of the 12 patients, 9 patients eventually met all inclusion/exclusion criteria. No related adverse events were reported for all 27 patients. Physician questionnaire results indicated that the physicians were satisfied with the ease of use of the system as well as its efficacy in keeping low cuff pressure sealing the trachea while reducing mechanical pressure and reducing VAP incidence. VAP was reported in one patient (11%) ventilated by the AnapnoGuard 100 system and in seven patients (70%) in the retrospective group.

This study was designed in order to evaluate the safety of the AnapnoGuard system in ICU patients ventilated for more than 12 hours. The possible complications this study aims to address are related to inappropriate cuff pressure in patients under prolonged ventilation. The complications may include mechanical complications as a result of over inflation of the cuff and leakage as a result of under inflation of the cuff. These measures are best identified and analyzed if a patient is intubated for more than 12 hours.

